Over 4 million South Africans are affected by diabetes; about 7% of the population, with as many as 41% of cases still undiagnosed (Health 24, 2016; IDF, 2015). Diabetes is responsible for 6% of the mortality in 2012 in South Africa (Alwan et al., 2011; WHO, 2014b). The epidemic of diabetes mellitus in South Africa is driven by obesity resulting from unhealthy lifestyles (Manyema et al., 2015). The Eastern Cape Province is not exempted from this menace. [name] et al. (2016) reported a high prevalence (24%) of diabetes among adults in one of the two largest municipalities (Buffalo City Metropolitan Municipality) in the Eastern Cape Province.

Diabetes mellitus is a disease characterised by an abnormally high blood glucose level (hyperglycaemia) (American Diabetes Association, 2011:1). Uncontrolled hyperglycaemia is often associated with a high risk of developing either microvascular or macrovascular health complications (Cade, 2008:1; Kirkman et al., 2012:3). Microvascular complications of diabetes include diabetic nephropathy, neuropathy and retinopathy, leading to kidney disease, amputation and blindness (Asif, 2014:1; Deshpande, Harris-Hayes & Schootman, 2008:3), while macrovascular complications include coronary artery disease, peripheral arterial disease, and stroke (Chawla, Chawla & Jaggi, 2016:3; Fowler, 2011:1). These complications further impose greater burden on the individual, reduce the quality of life, increase the risk of premature mortality and impact enormous burden on the healthcare system (Nolan, Damm & Prentki, 2011:1).

However, diabetes mellitus is treatable, though cannot be cured, except for the recently proposed surgical intervention, specifically gastric bypass (Eenfeldt, 2015). Various treatments allow most individuals with diabetes to live relatively stable and normal lives (Asif, 2014:1; Diabetes UK, 2017). Intensive therapy for patients with diabetes mellitus delays the onset and as well slows the progression of clinically important complications such as retinopathy, including vision-threatening lesions, nephropathy and neuropathy by a range of 35 or more than 70% (The Diabetes Control and Complications Trial Research Group, 1993).

Blood glucose control indicated by a reduction in the HbA1c level is accompanied by a reduction in the risk of complications (American Diabetes Association, 2011; 9). As low as 1% reduction in HbA1c  has been reported to be associated with a 21% reduction in the risk of any end-point death related to DM, 14% reduction in the risk of developing myocardial infarction as well as 37% reduction in micro-vascular complications (ACCORD Study Group, 2010; Ismail-Beigi et al., 2010:1; Stratton et al., 2000).

However, in spite of the innovative scientific discoveries and treatment modalities, it seems that treatment outcomes of individuals with diabetes are generally suboptimal. Diabetes control in developed countries is below average (Teoh et al., 2010). Also, diabetes control in sub-Saharan Africa (SSA) is generally suboptimal (Camara et al., 2015:3). The prevalence of uncontrolled diabetes range from 62% in Nigeria (Ngwogu et al., 2014), 68% (Congo) (Longo-Mbenza et al., 2008), 70.5% (Saudi Arabia) (Khan et al., 2014), 79.2% (Uganda) (Kibirige et al., 2014) to 82% in Botswana (Mengesha, 2007). Similarly, sub-optimal control of DM has been noted in South Africa (Folb et al., 2015:4; Webb, Rheeder & Van Zyl, 2015:6). The prevalence of sub-optimal control in various provinces of South Africa ranges from 69.3% in Northwest (Kadima & Tumbo, 2013), 81% in Cape Town (Daramola, 2012), 83% in Kwazulu-Natal (Igbojiaku et al., 2013) to 84% in Eastern Cape Province (Adeniyi et al., 2016). This indicates a higher prevalence of uncontrolled diabetes in South Africa, compared to other countries in SSA with Eastern Cape Province, with the highest prevalence in South Africa.

Various reasons have been documented to be responsible for this poor glycaemic control. Such factors include duration of disease (Khattab et al., 2010:1; Nemeh, Yousef & Aysha, 2011:3) and comorbidity (Woldu et al., 2014:3). Other factors include overburdened healthcare facilities, insufficient health education, sub-optimal knowledge and beliefs, poor support structures, unsafe communities and low income (International Diabetes Federation 2016; Kibirige et al., 2014). However, a major causative factor of poorly controlled diabetes among individuals with diabetes is non-adherence to treatment regimen and recommended lifestyle changes for the diabetic patients (Aikens & Piette, 2013:1; Davies et al., 2013:9; de Vries et al., 2014:3; Hamine et al., 2015:1; Jarab et al., 2014:1; Kassahun, Eshetie & Gesesew, 2016:3). There are wide range of documented evidences of non-adherence to treatment among individual with diabetes both globally and nationally (Mann et al., 2009; Krishna & Boren, 2008; Mbuagbaw et al., 2012; Rwegerera, 2014).

Non-adherence to medication among patients has long been recognised as a pressing problem in South African primary healthcare system (Kagee, 2004). Patients are the centre of the healthcare team and the importance of increasing their knowledge base on diabetes has been documented to influence diabetes self-management (Amod et al., 2012; Mandewo et al., 2014; Santos et al., 2015). Viewed in this perspective, there is a need for interventions to enhance patient’s education and improve their self-treatment behaviours and self-management skills. Limited control trials of various interventions have been conducted among diabetic patients in order to determine their effectiveness in boosting patients’ knowledge and self-care behaviours. Such interventions include educational programmes using various media as well as lifestyle interventions (Berg et al., 2009; Mash et al., 2012; Schwellnus et al., 2009). However, there is limited documented interventional research available to address the correlates of uncontrolled diabetes in South Africa.

The use of information and communication technology such as computers, mobile phones, satellite communications, patient’s monitors among others to support health services and information exchange are available (Hamine et al., 2015:1; Wiggins, 2015:88). Of course, mobile technology has the potential to improve the quality, safety and efficiency of healthcare services, and to impact almost every aspect of health sector (Cole-Lewis & Kershaw, 2010; Jemberu, 2013). The World Health Organisation also prioritised the use of new technologies to assist healthcare delivery in resource-limited settings (Joint United Nations Programme on HIV/AIDs, 2005; WHO, 2011). The most widely used technology is the mobile phones, with an evidence of increasing uptake in Africa (Lester et al., 2006; Sinha & Barry, 2011). The use of mobile phones has been shown to have the potential to radically improve healthcare in the most remote and resource-poor environments of the world (Hamsphire et al., 2015:1; Marwaha, 2010). Even before phones became mobile, Hyanes et al. (1996) had already posited that communication effort that would keep the patients engaged in healthcare may be the simplest and most-cost-effective strategy for improving adherence to chronic medications. The use of mobile phones has been documented to improve treatment adherence, appointment compliance and developing support networks for health workers (Hall et al., 2014). Likewise, the use of SMS on the mobile phones is recognized as a means of providing new and innovative opportunities for disease prevention efforts at a low cost (International Diabetes Federation, 2016).

Various randomised controlled trials on the use of SMS has been conducted in various parts of the world including Africa; and found to be cost-effective and associated with an improvement in self-management behaviour, lifestyle changes, medication compliance and improved blood glucose control among the study participants (Carole et al., 2012; Dobson et al., 2016; Ferrer-Roca et al., 2004; Jemberu, 2013; Jha et al., 2015:4; Islam et al., 2014; Mohammed et al., 2014).

There is a rapid increase in the use of mobile phones in South Africa; and are more affordable and available now (Leon, Schneider, Daviaud, 2015:4). Also, in South Africa, successes have been recorded with the use of mHealth technology among patients with various conditions such as hypertension (Leon et al., 2015), sexually transmitted infections (STIs) and HIV/AIDS (de Tolly, Nambaware & Skinny, 2011:1, malaria (Quan et al., 2014:5) and maternal and child health conditions (Baron et al., 2016:4). However, there is little or no documented interventional studies applying the use of mHealth technology strategy for diabetes control among individuals with diabetes (Leon et al. 2015; Lunny et al., 2014). Thus, there is need to carry out interventional studies targeting the use of mHealth among diabetic individuals.

1. **PROBLEM STATEMENT**

Despite the effectiveness of drug therapy in diabetes management, high rate of poor adherence persists among diabetic patients, both globally and nationally (Adisa & Fakeye, 2014; Bagonza et al., 2015; Cramer, 2004; Mann et al., 2009). A surge in the prevalence of diabetes has been documented in South Africa with an increasing disease burden and mortality associated with it (IDF, 2015). South Africa has the second highest prevalence of diabetes in Africa (Guarigata et al., 2013:3). Also, glycaemic control among diabetic patients in South Africa appears to be a challenging task for healthcare professionals (Shilubane, 2010). This is likely to be consequential to the documented poor adherence to medication among diabetic patients attending the primary healthcare facilities (Booysen & Schlemmer, 2015; Kagee, 2004); as intensive medication therapy and compliance with the prescribed medication regimen is a key factor for glycaemic control. Consequently, there is a resultant predisposition to complications development leading to poor quality of life, disability, premature mortality and excessive burden on the individuals; thus placing significant strain on the already overburdened healthcare system.

mHealth is an emerging and a cost-effective measure proven to be effective in improving patient’s self-management behaviours, drug regimen adherence and appointment compliance. However, the effectiveness of mHealth among diabetic patients has rarely been documented in South Africa, and more specifically, in an economically poor region of the Eastern Cape Province. Hence, the need for an interventional study to determine the efficacy of mHealth technology, aside the usual care in promoting glycaemic control and adherence to anti-diabetic therapy among individuals with diabetes in a low-resource setting.

1. **AIM AND OBJECTIVES**

The overall aim of this interventional study is to determine the efficacy, acceptability and feasibility of the mHealth technology in promoting adherence to anti-diabetic therapy and glycaemic control among diabetic patients in low resource areas of the Eastern Cape Province, in order to inform public health direction concerning diabetes control.

1. **OBJECTIVES**

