**The specific objectives of the study are:**

- Determine the efficacy and acceptability of mobile phone SMS in promoting glycaemic control among individuals living with diabetes in the Eastern Cape Province.
- Determine the efficacy and acceptability of mobile phone SMS in promoting adherence to medication, physical activity and recommended diets among individuals living with diabetes in the Eastern Cape Province.
- Determine the effectiveness of the use of mobile phone SMS as a clinic appointment reminder or awareness promoter about diabetes and its complications.
- Determine the efficacy of the use of mobile phone SMS in improving diabetes knowledge among individuals living with diabetes in the Eastern Cape Province.
- Determine the healthcare providers’ perspective on the use of mHealth technology in diabetes control in the Eastern Cape Province; and
- Determine the efficacy of text messaging in improving other secondary clinical outcomes (body weight, blood pressure and body mass index).

1. **RESEARCH QUESTIONS**

- Would the use of mobile phone SMS be effective in promoting glycaemic control among individuals living with diabetes?
- Would the use of mobile phone SMS be effective in promoting adherence to medication, physical activity and dietary recommendations among individuals living with diabetes?
- Would the use of mobile phone SMS be effective in promoting diabetes knowledge among individuals living with diabetes?
- How effective is the mobile phone SMS as a clinic appointment reminder and awareness promoter on diabetes and its complications?
- What are the likely barriers to the use of SMS in conveying health information to persons living with diabetes in the Eastern Cape Province?
- How do the healthcare providers perceive mHealth technology as a feasible option in the control of diabetes?

1. **SIGNIFICANCE OF THE STUDY**

Poor adherence to anti-diabetic therapy has been identified as a threat to effective glycaemic control as well as prevention of complications among individuals living with diabetes. Since diabetes is chronic in nature, patient’s involvement in their care as well as improvement in their self-care management behaviour will go a long way in improving their quality of life.

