Also, improving adherence to anti-diabetic therapy will play a key role in reducing morbidity and mortality related to diabetes. It is believed that the SMS services have the potential to build awareness about the disease, improve self-management and prevent complications also in resource-limited settings. Since the SMS trials has been documented to be effective in other countries and for certain other diseases, the findings of this study might help to determine if this same measure can be applied to those in the low-resource areas, and if it will yield any positive result. If this intervention proves to be efficient in the current study, large-scale implementation could be undertaken across all the diabetes clinics in the province and in the country at large.

Finally, the findings of this study will help the policy makers to understand the importance of creating healthcare systems that better meets the need of people and develop prevention and management strategies for diabetes and other chronic diseases using innovative mobile phone technologies at the national level.

1. **SCOPE AND DELIMITATION**

The study is delimited to adults who were already diagnosed of diabetes, receiving anti-diabetic therapy and are attending the selected diabetes clinics in the Eastern Cape Province. Variables of interest will be mhealth technology (SMS) and diabetes control among individuals living with diabetes.

1. **DEFINITION OF KEY OPERATIONAL TERMS**

**Efficacy**: It is defined as the ability of the mHealth intervention to produce intended results; that is, enhancing self-management, promotion of medication adherence, and glycaemic control among diabetic individuals.

**Acceptability**: It is defined as the acceptance of the mHealth intervention by the diabetic individuals.

**Feasibility**: It is the ability to carry out the mHealth study among the diabetic individuals.

**Adherence**: In this study, adherence means sticking to the prescribed anti-diabetic therapeutic regimen by diabetic individuals.

**mHealth**: An abbreviation for mobile health. It is the use of mobile devices, specifically, SMS, to support and promote diabetes control.

**Glycaemic control**: It is the regulation and maintenance of blood glucose levels within normal range.

**Therapy**: The treatment and management of diabetes mellitus; including medical and lifestyle management.

**Anti-diabetic therapy:** Administration of drugs, diets and exercise in order to reduce blood glucose level.

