**16. DATA COLLECTION AND INTERVENTION**

Both intervention and the control groups will continue with their usual care including all medical visits, tests, and diabetes support programmes. In addition, the intervention group will receive SMS at an agreed time and days of the week tailored according to their needs, goals and their care plan. Participants will as well receive motivational and support messages and they can opt to receiving additional messages on topics such as lifestyle intervention; diets, physical activity and smoking cessation. Where appropriate to their care, patients will also receive reminders to check their blood glucose levels, insulin or drug use. Contacts to be reached in case of any query will be provided at the end of the message. Call records will be kept.

Data will be collected at baseline, and six months after the intervention. Baseline data will include demographic characteristics including duration of diabetes, behavioural factors (smoking, physical inactivity, alcohol use), anthropometric measurements (weight, height, waist and hip circumferences) and biochemical measurements (random blood sugar). At baseline, the demographic characteristics, particularly, age, and duration of diabetes as well as mean blood sugar will be balanced between both arms.

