**18. SECONDARY OUTCOME MEASURES**

The secondary outcome measures will be assessed at three and six months namely;

- Knowledge on diabetes which will be obtained with the validated Michigan Diabetes Knowledge Test Questionnaire-2 (Fitzgerard et al., 2016).
- Medication adherence, using a pre-validated self-developed medication adherence questionnaire.
- Clinic attendance, using clinic registers.
- Quality of life, using the EQ-5D self-perceived quality of life questionnaire (EURO-QOL Group, 2009).
- Barriers to SMS intervention and the healthcare providers’ perception about SMS use using a self-designed questionnaire.
- Clinical (hypertension, overweight/obesity) and behavioural outcomes (Smoking, alcohol use, and physical activity) will be measured using the WHO modified STEPwise approach.
- Factors affecting adherence to diabetes therapy using a self-designed questionnaire

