**19. SMS DEVELOPMENT AND DISPERSAL**

The messages will be developed by a team involving the principal investigator, supervisor, general physicians, endocrinologists and a nurse. Also, health education materials from the National Diabetes Education Programme will be used. Once the messages have been developed, they will be sent to several individuals including those with no formal education in order to ascertain its simplicity. The questions will be developed based on the principles of the behavioural change theory (Leventhal & Cameron, 1987). SMS will be dispersed to all participants in the intervention arm on a daily basis over the period of study at an agreed time of the day.

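### Patient acceptability is part of the aim and of two objectives but has no listed measure, feasibility has no named metric, and sections 16 and 19 of the protocol contradict each other on SMS frequency

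*Protocol*

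**What the plan says.** **Aim, objectives and definitions.** Under Aim and Objectives, and again in section 11, the protocol sets out to "determine the efficacy, acceptability and feasibility of the mHealth technology". The first specific objective reads "Determine the efficacy and acceptability of mobile phone SMS in promoting glycaemic control", and the second attaches the same pair of terms to adherence. Under Definition of Key Operational Terms, acceptability is given as follows: "It is defined as the acceptance of the mHealth intervention by the diabetic individuals". Feasibility is given as: "It is the ability to carry out the mHealth study among the diabetic individuals". Neither definition comes with an instrument, a metric or a threshold.

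**Outcomes.** Section 17 makes change in random blood glucose the primary outcome. Section 18 lists knowledge, medication adherence, clinic attendance, quality of life, clinical and behavioural outcomes, and factors affecting adherence. It has one SMS-specific item, which covers barriers to the SMS intervention and the healthcare providers' "perception about SMS use using a self-designed questionnaire". The Research Questions ask about likely barriers to SMS, and about how providers "perceive mHealth technology as a feasible option in the control of diabetes".

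**Message schedule.** Section 16 says that "the intervention group will receive SMS at an agreed time and days of the week", tailored to the participant, with optional further messages and, where appropriate, reminders. Section 19 says that "SMS will be dispersed to all participants in the intervention arm on a daily basis". Section 15 has participants in the intervention arm asked for their preferred time of receipt and does not mention days. Section 16 provides for call records. Section 25 budgets nurses to dispatch messages and follow up for six months.

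**The concern.** There are two separate problems.

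The first is an objective without an outcome. A protocol that puts acceptability in its aim and in two of its objectives, and defines whose acceptance it means, should say what will be measured, in whom and when. Otherwise the trial could finish with no planned estimate of how many intervention participants accepted the messages. An analysis plan cannot repair this afterwards, because acceptance has to be asked of participants while they are in the study. Eligibility in section 13.1 also admits people who depend on a relative to read their messages, so reading cannot be taken for granted. The protocol foresees wide roll-out if the intervention works, and acceptance would bear on that decision.

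The second is that the SMS is the only component separating the two arms, and its frequency is described in two incompatible ways. Staff working from section 16 and staff working from section 19 could deliver different interventions under one arm label.

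**Working it through.** The protocol states no figure on this point, so there is none to reproduce. The check is a comparison of passages, followed by simple counting.

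**Step 1: from aim to outcome.**

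| Concept | Where promised | How defined | Listed measure |
|---|---|---|---|
| Acceptability | Overall aim; objectives 1 and 2; section 11 | Acceptance by the patients | None in sections 17 or 18 |
| Feasibility | Overall aim; section 11 | Being able to carry out the study | None named; provider perception in section 18 relates to it |

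The barriers and provider item does not close the acceptability gap. Providers' views are not patients' acceptance. A list of obstacles shows what hinders use but gives no proportion of participants who accepted the messages. The baseline data in section 16 and the end-of-intervention assessments in section 10.2 contain no acceptability measure either.

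Feasibility is in a better position. A research question treats it through providers' perception. Recruitment can be read against the target of 108 per arm, and retention against the 20% loss assumed in section 14. None of these is named as a feasibility metric.

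**Step 2: the two schedules.** If every participant in the intervention arm receives messages every day, there are no days left to agree. Section 16 has days agreed; section 19 does not. They coincide only if every participant agrees to all seven days.

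**Step 3: how far apart the schedules can be.** Inputs: a duration of six months (section 11), taken as 26 weeks, which is an assumption; 108 participants in the arm (section 14); days per week of 7 under section 19. Section 16 gives no number of days, so the whole range from 1 to 7 is shown.

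Messages per participant = days per week × 26. Arm total = that × 108.

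| Days per week | Per participant | Arm total | Daily count ÷ this count |
|---|---|---|---|
| 1 | 26 | 2,808 | 7.0 |
| 2 | 52 | 5,616 | 3.5 |
| 3 | 78 | 8,424 | 2.3 |
| 5 | 130 | 14,040 | 1.4 |
| 7 (section 19) | 182 | 19,656 | 1.0 |

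The count assumes one message per sending day. Opt-in messages and reminders would add an unspecified number under either schedule.

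**The case against.** The strongest reply is that the protocol is not silent on either concept. Section 18 has a questionnaire on barriers to SMS and on providers' perception. The Research Questions tie provider perception to feasibility and ask about barriers among people with diabetes. Feasibility, defined as being able to carry out the study, is largely visible from recruitment and retention, which the trial will produce in any case. The questionnaire is self-designed and its items are not shown, so it may contain acceptance questions. The intention-to-treat comparison of glucose can be interpreted without any process measure.

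Much of this stands, and it rules out several stronger readings:

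- A reader might infer that two of the three parts of the aim are beyond answering. That does not follow. Feasibility is partly informed by what is planned, and what is missing there is a stated metric.
- A reader might infer that message delivery and opt-outs will go unrecorded. The protocol says that call records will be kept; it does not say that nothing else will be. It specifies no message log, which is a different statement.
- A reader might infer a sure several-fold difference between the two schedules. The number of agreed days is not given, and at seven days the difference vanishes.
- A reader might infer that a stated delivery outcome lacks its denominator. The protocol lists no such outcome, so an unsettled schedule would affect a delivery measure only once one is added.

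The reply does not supply a measure of patient acceptance. A possible item in an unseen questionnaire is not a listed outcome, and the item as described covers barriers and providers. Nor does the reply reconcile sections 16 and 19.

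**Conclusion.** The point holds in two limited parts.

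1. Patient acceptability, as the protocol defines it, has no listed measure although it is in the overall aim and in two specific objectives. Feasibility is a lesser gap: it is partly informed but has no named metric. This conclusion rests on the text of sections 17 and 18 and on the protocol's own definitions.
2. Sections 16 and 19 contradict each other on SMS frequency. Under the assumptions of 26 weeks and one message per sending day, the planned count is 182 per participant by section 19 and anything from 26 to 182 by section 16. The gap runs from none to 7-fold, and the protocol gives no basis for narrowing it.

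This should be corrected, but it does not prevent the primary comparison. What is affected is one stated objective and the description of the intervention that is being tested.

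**What to change.** **In section 18, add an acceptability outcome for the intervention arm at six months.** It should give the proportion of participants who report that they read most messages, or had them read to them by a relative, and who wish to continue, together with the proportion who opted out. The wording about a relative is needed because section 13.1 admits such participants. For illustration, with about 86 completers (108 × 0.8 = 86.4) and an assumed acceptance of 80%, the 95% confidence interval half-width would be 1.96 × √(0.8 × 0.2 / 86) = 0.085, or about 8.5 percentage points.

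**Name the feasibility metrics.** These would be recruitment, retention, and messages delivered out of messages planned, the last taken from a per-participant log kept by the dispatching nurses. State whether opt-in messages and reminders count as planned.

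**Reconcile sections 16 and 19 to one stated SMS schedule.** Which schedule it should be is for the investigators to decide; this review takes no position.

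**Cost.** A few more questionnaire items at the six-month assessment that is already planned, a log kept by nurses already in the budget, and slightly more data entry. The sample size and the primary analysis do not change.
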